## Abstract

**Introduction:**

Mild cognitive impairment (MCI) is a prodromal stage to dementia, affecting up to 20% of the aging population worldwide. Patients with MCI have an annual conversion rate to dementia of 15–20%. Thus, conditions that increase the conversion from MCI to dementia are of the utmost public health concern. The COVID-19 pandemic poses a significant impact on our aging population with cognitive decline as one of the leading complications following recovery from acute infection. Recent findings suggest that COVID-19 increases the conversion rate from MCI to dementia in older adults. Hence, we aim to uncover a mechanism for COVID-19 induced cognitive impairment and progression to dementia to pave the way for future therapeutic targets that may mitigate COVID-19 induced cognitive decline.

**Methodology:**

A prospective longitudinal study is conducted at the University of Oklahoma Health Sciences Center. Patients are screened in the Department of Neurology and must have a formal diagnosis of MCI, and MRI imaging prior to study enrollment. Patients who meet the inclusion criteria are enrolled and followed-up at 18-months after their first visit. Visit one and 18-month follow-up will include an integrated and cohesive battery of vascular and cognitive measurements, including peripheral endothelial function (flow-mediated dilation, laser speckle contrast imaging), retinal and cerebrovascular hemodynamics (dynamic vessel retinal analysis, functional near-infrared spectroscopy), and fluid and crystalized intelligence (NIH-Toolbox, *n*-back). Multiple logistic regression will be used for primary longitudinal data analysis to determine whether COVID-19 related impairment in neurovascular coupling and increases in white matter hyperintensity burden contribute to progression to dementia.

## 1. Introduction

Mild cognitive impairment (MCI) is an age-related neurocognitive disorder characterized by absence of dementia, and subjective and objective minimal cognitive impairments [1,2]. Recent meta-analyses of community dwelling older adults reported a 17.3% overall pooled prevalence of MCI [3], with increasing prevalence associated with age [4]. MCI is a prodromal stage to dementia [5–7] with an annual conversion rate of MCI to dementia ranging between 3–4.9% in community settings, up to 18% in specialty clinics, and 23.8% in socioeconomically disadvantaged areas [7–10]. Dementia is characterized with impairments in executive function, memory, language, and behavior, affecting up to 55 million individuals annually, markedly impairing patients quality of life and ability to perform everyday activities [11]. Significant physical, psychological, social, and economic burden is placed on patients with dementia, as well as their caregivers, families, and society at large [12,13]. Due to the immense number of individuals affected by this disease, risk factors known to increase the conversion rate of MCI to dementia (e.g., diabetes, hypertension, atherosclerosis) have enormous public health relevance [14–17].

The COVID-19 pandemic has caused significant morbidity and mortality globally, with over 103 million cases in the United States alone, as of June 1^st^, 2023. It is important to note that COVID-19 predominantly causes mortality in older adults [18–20]. Evidence suggests that COVID-19 increases the conversion rate of MCI to dementia in older individuals compared to those with no previous diagnosis of COVID-19 [21]. Acute COVID-19, and long-term effects after recovery, have been linked to a range of cerebral small vessel complications, including ischemic damage to the white matter, lacunar stroke, microhemorrhages, and cognitive dysfunction [22–24]. However, the mechanistic link between COVID-19 and the increased risk of progression from MCI to dementia remains unclear. Emerging clinical and basic science evidence suggests that SARS-CoV-2 infects endothelial cells[25], causing downstream inflammation and oxidative stress, which contributes to generalized macro- and microvascular endothelial dysfunction acutely, and following recovery of infection [26]. This dysfunction extends to the cerebrovascular circulation and has been linked to induction of cerebromicrovascular pathologies known to contribute to vascular cognitive impairment and dementia [22]. Hence, COVID-19 has detrimental effects on the cerebrovasculature, which is critical for maintaining normal cognitive function [27].

Components of the neurovascular unit, specifically the cerebromicrovascular endothelium, play a critical role in maintaining normal cognitive function, with adequate oxygen and nutrient delivery achieved through the homeostatic mechanism of neurovascular coupling (NVC) [28–31]. NVC is responsible for adjustment of local cerebral blood flow through endothelium-dependent cerebromicrovascular dilation to match the increased metabolic needs of active brain regions [32]. Preclinical evidence in aged animals demonstrate that impairment of NVC responses and cerebromicrovascular endothelial function is causally related to cognitive decline, while improvement of NVC responses via pharmacological means is associated with restored cognitive performance [33–39]. Importantly, in human trails these findings have been corroborated with cognitive impairment in aging and age-related diseases being strongly associated with impaired NVC [40–43]. However, whether deteriorating cognitive function associated with COVID-19 is causally related to impairments in NVC is unknown.

In this study, our primary aim is to establish a mechanistic link between COVID-19 and the progression of MCI to dementia. To accomplish this objective, we will utilize a comprehensive and integrated battery of vascular measurements, encompassing the quantification of small vessel ischemic damage through magnetic resonance imaging (MRI), assessment of NVC responses and endothelial function, and analysis of serum markers related to vascular disease. By examining the correlation between these measurements and COVID-19, our study aims to yield valuable insights into the underlying mechanisms that drive this progression.

## 2. Study aims and protocol

### 2.1 Study aims

To determine whether history of COVID-19 infection in patients with MCI disrupts systemic endothelial function and impairs NVC response compared to MCI patients with no history of COVID-19 infection.To determine whether history of COVID-19 infection aggravates the impairment of fluid cognitive abilities in patients with MCI.To determine whether impairment of NVC responses in recovered COVID-19 patients with MCI contributes to increased conversion of MCI to dementia.To determine whether COVID-19 related increases in white matter hyperintensity (WMH) burden contribute to conversion of MCI to dementia.

### 2.2 Study design

This study will test the hypothesis that COVID-19 infection promotes systemic endothelial dysfunction, impairing NVC responses and promoting white matter damage, contributing to the progression of MCI to dementia. To test this hypothesis, we will prospectively follow patients, who are diagnosed with MCI, with or without history of SARS-CoV-2 infection, for 18 months. The timeline for study design and investigative measurements are represented in **Fig 1.** Study participants will be evaluated for eligibility and enrolled through neurology clinics at the University of Oklahoma Health Sciences Center (OUHSC) and Oklahoma City Veterans Affairs (VA) Medical Center (Visit 0). Upon enrollment, patient history, demographic data, standard risk factors for dementia, cognitive status and WMH status (MRI scan) will be recorded. Blood collection, cognitive tests (NIH-toolbox, *n-*back), and baseline physiologic assessments for peripheral endothelial function (flow-mediated dilation [FMD], laser speckle contrast imaging [LSCI]) and NVC responses (functional near-infrared spectroscopy [fNIRS], dynamic retinal vessel analysis [DVA]) will be conducted at the OUHSC Translational Geroscience Laboratory (Visit 1). Study participants will undergo semi-annual clinical neurologic evaluations as a part of standard care. In addition to COVID-19 status since enrollment (e.g., PCR+/-, symptoms), progression from MCI to dementia will be assessed by the clinical neurology team with final adjudication made through consensus management conferences. Repeat of all physiological assessments, cognitive tests, and serum collection will be performed at month 18 (Visit 2), and the second MRI scan will be performed. If some participants decide to terminate their participation in the study for any reason, they will be invited to an early termination visit, which will include the same evaluations as in Visit 2.

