### 2.7 Primary outcome

The primary outcome of interest is whether COVID-19 contributes to the progression of MCI to dementia through impairment of NVC response, and promotion of white matter damage. Diagnosis of MCI and progression to dementia will be made clinically through the OUHSC Department of Neurology. Trained investigators will perform NVC measurements (fNIRS, electroencephalography [EEG], DVA) at baseline and 18 months follow-up. Burden of white matter damage (WMH) will be neuroradiologically assessed by the clinical neurology and neuroradiology team at baseline (at diagnosis of MCI prior to COVID-19 pandemic) and 18-month follow-up.

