**Comorbidities**	Demographic	Past medical history and/or ongoing medically controlled for conditions	Nominal
**SARS-CoV-2 Variant**	Demographic	Estimated variant based on time (month and year) patient was infected with SARS-CoV-2	Nominal
**Vaccination History**	Demographic	Number of doses, vaccine manufacturer	Nominal
**Education**	Demographic	Highest level of education obtained	Ordinal
**Progression of MCI to dementia**	Clinical diagnosis	Use of neurocognitive screening (e.g., MoCA, clinical dementia rating) and final adjudication made through consensus management	Binary
**COVID-19 status**	*Previously confirmed COVID-19 history	COVID-19 positive or COVID-19 negative	Binary
**Sex**	Demographic	Male or female	Binary

Note. Neurovascular coupling (NVC), Functional near-infrared spectroscopy (fNIRS), Oxy-hemoglobin (HbO), Electroencephalography (EEG), Dynamic retinal vessel analysis (DVA), Laser speckle contrast imaging (LSCI), Flow mediated dilation (FMD), Hydroxyl radical antioxidant capacity assay (HORAC), White mattery hyperintensity (WMH), Montreal cognitive assessment (MoCA), Mild cognitive impairment (MCI), Adverse childhood experience (ACE).

* Indicates COVID-19 was confirmed by PCR or serologic testing.

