### 2.10 Data collection process

Patients who have consented to the study are interviewed for demographic information (sex, age, race education), COVID-19 history (symptoms during infection, and symptoms without confirmed infection), COVID-19 vaccine history, medical history (oncological, genitourinary, gastrointestinal, respiratory, endocrine, neurological, cardiovascular, musculoskeletal, and psychological conditions), screened for DVA (eye surgery history, photosensitive epilepsy, glaucoma, allergies to tropicamide), and social history (previously or current use of tobacco, alcohol, and recreational drugs, and adverse childhood experiences). Medication list is obtained from all patients, and common age-related conditions (i.e., hypertension, diabetes) must be pharmacologically controlled. All patients enrolled have baseline MRI data with neuroradiologic report at MCI diagnosis. Every 6 months patients have repeat neurocognitive screening and evaluation through OUHSC Department of Neurology faculty to identify if patients have progressed from MCI to dementia. Physiologic, circulating factors, and cognitive data is obtained from patients at visit one and at 18-month follow-up. Patients are scheduled through the Department of Neurology for a second MRI to obtain neuroradiologic report at 18-month follow-up after visit one.

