#### 3.1.2 Neuroimaging investigations

Prior to visit one, patients were diagnosed with MCI and neuroradiologically (i.e., MRI) assessed for small vessel complications. In a recent meta-analysis from Guo and Shi, small vessel ischemic damage to the brain, evidenced by white matter hyperintensities (WMH) on MRI, was associated with increased risk of development of MCI and dementia [50]. Ischemia localized to, and originating from small vessels, and microbleeds are two common pathologies in cerebral small vessel disease (CSVD) [51], and can be imaged by MRI through T2 fluid attenuated inversion recovery (FLAIR) and T2* gradient echo (GRE) or susceptibility weighted imaging sequences (SWI), respectively. All study participants, in addition to the first MRI scan performed as a point of care before enrollment into the study, will be neuroradiologically evaluated at Visit 2 using a 3T MRI. Increased burden of WMH (i.e., confluence of deep foci and extension of periventricular WMH into the deep white matter) are one of the most common manifestations on T2 FLAIR MRI imaging for diagnosis of CSVD [52] and is associated with acute and recovered COVID-19 patients [22]. Moreover, burden of WMH, determined by Fazekas scale [53], will be longitudinally assessed as a contributing factor for conversion of MCI to dementia in COVID-19 patients. The Fazekas scale grades the periventricular and deep white matter from 0–3, depending on the size and confluence of the lesions [53,54]. This grading system is the most widely used system to date to identify severity of white matter pathology [53,55]. Additionally, presence of microbleeds will be neuroradiologically assessed, as this pathology is also associated with COVID-19 and has a specific pattern of distribution that distinguishes CSVD burden in recovered and acute COVID-19 patients from other known causes (i.e., hypertension, acute respiratory distress syndrome) [22].

WMH burden will be evaluated at baseline by Fazekas scale to determine if there are differences at diagnosis that could influence results at cross-sectional cognitive and physiological measurements. Longitudinally, WMH burden will be calculated at 18-months to determine the influence of WMH on progression to dementia and whether COVID-19 increases burden of WMH in patients with MCI.

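### Progression to dementia is judged by the team that also assesses COVID-19 status, and no masking is described at the consensus conference or the month-18 MRI read

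*Protocol article*

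**What the plan says.** All references are to the protocol article.

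- **Who assesses exposure and outcome.** Section 2.2: "In addition to COVID-19 status since enrollment (e.g., PCR+/-, symptoms), progression from MCI to dementia will be assessed by the clinical neurology team". A consensus conference then takes the final decision on progression.
- **Where the diagnosis is made.** Section 2.7: "Diagnosis of MCI and progression to dementia will be made clinically through the OUHSC Department of Neurology". Section 2.10 gives the frequency: "Every 6 months patients have repeat neurocognitive screening and evaluation through OUHSC Department of Neurology faculty".
- **How progression is defined.** Table 1 (section 2.9) lists it as a binary clinical diagnosis: "Use of neurocognitive screening (e.g., MoCA, clinical dementia rating) and final adjudication made through consensus management". The instruments are examples and no cut-off is given.
- **Who assesses WMH.** Section 2.7 says that WMH burden "will be neuroradiologically assessed by the clinical neurology and neuroradiology team at baseline (at diagnosis of MCI prior to COVID-19 pandemic) and 18-month follow-up". Section 3.1.2 names the scale: "The Fazekas scale grades the periventricular and deep white matter from 0–3". Section 2.10 schedules the second MRI through the Department of Neurology, at 18 months after visit one.
- **How these enter the analysis.** The primary longitudinal model in section 4.2 relates progression to COVID-19, NVC, change in WMH burden and their interactions with group.

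The article does not say that the conference or the MRI readers are masked to anything. The Discussion names loss to follow-up and confounding as limitations, but not knowledge of exposure when the outcome is assessed.

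**The concern.** A team cannot be masked to something it assesses itself. The study's hypothesis is that COVID-19 drives conversion, and conversion is decided by judgement in patients who by definition already lie near the boundary. If infection history affects how borderline cases are labelled, the error rate differs between the groups being compared. Such an error can create, enlarge, shrink or hide an association, and adjusting for covariates does not remove it.

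The same applies to the WMH pathway. Clinical neurology makes the dementia diagnosis and shares the WMH assessment. At month 18 an assessor could therefore have the new MRI report in hand when deciding on dementia, or know the diagnosis when grading the scan. Aim 4 asks whether WMH burden contributes to conversion, so the two measurements need to be made independently of each other.

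**Working it through.** **1. What is stated and what is inferred.**

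| Link | Status in the article |
|---|---|
| Assessing team knows infection status since enrolment | Stated (2.2) |
| Assessing team knows COVID-19 history before enrolment | Likely: enrolment is through the neurology clinics and patient history is recorded then (2.2). But 2.10 does not name who takes the COVID-19 history |
| Consensus conference knows COVID-19 status | Inferred: membership and materials are not described |
| Clinical neurology takes part in the WMH assessment | Stated (2.7), jointly with neuroradiology |
| Month-18 reader knows COVID-19 or dementia status | Possible; nothing described prevents it |

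**2. Which measurements are exposed, by timing.**

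- Baseline MRI: section 2.7 places it at MCI diagnosis before the pandemic. A read made then cannot reflect COVID-19 status; a later re-read could.
- Diagnoses at months 6 and 12: these precede the month-18 MRI, so that scan cannot influence them. They can still be influenced by knowledge of infection, and a diagnosis already made can be known to the month-18 reader.
- Month 18: diagnosis and Fazekas grade can each inform the other.
- Cross-sectional primary outcome in 4.1 (fNIRS): instrument-based and not touched by this point.

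**3. The plan's own figures.** Section 2.4 gives 10/18 = 55.6% against 23/100 = 23%, p = 0.011. The continuity-corrected chi-square is 118 × (|10×77 − 8×23| − 59)² / (18×100×33×85) = 118 × 527² / 5,049,000 = 6.49, p = 0.0108. The stated value reproduces.

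**4. Illustration of size.** From the document: 23%, the never-infected rate. Assumed: true conversion is 23% in both groups, controls are labelled without error, and the mislabelled share is 5%, 10% or 15%.

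Over-diagnosis: a share x of COVID+ non-converters is labelled dementia, so p₁ = 0.23 + 0.77x. Under-diagnosis: a share x of COVID+ converters is not labelled, so p₁ = 0.23(1 − x). In both cases OR = [p₁/(1 − p₁)] / (0.23/0.77), and 0.23/0.77 = 0.2987.

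| x | Over: p₁ | Odds | OR | Under: p₁ | Odds | OR |
|---|---|---|---|---|---|---|
| 5% | 0.2685 | 0.367 | 1.23 | 0.2185 | 0.280 | 0.94 |
| 10% | 0.3070 | 0.443 | 1.48 | 0.2070 | 0.261 | 0.87 |
| 15% | 0.3455 | 0.528 | 1.77 | 0.1955 | 0.243 | 0.81 |

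**5. Effect on the error rate, over-diagnosis case.** Assumed: an unadjusted two-sided 5% test of two proportions, with all 200 patients analysed. With d = p₁ − 0.23, SE₀ the pooled and SE₁ the unpooled standard error, P(reject) = Φ((d − 1.96·SE₀)/SE₁) + Φ((−d − 1.96·SE₀)/SE₁).

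For x = 10% and 100 per group: d = 0.077, SE₀ = 0.0627, SE₁ = 0.0624. The first term is Φ(−0.73) = 0.231 and the second is about 0.001, so P = 23.2%.

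| x | 1:1 split | 18:100 split |
|---|---|---|
| 0 | 5.0% | 5.0% |
| 5% | 9.6% | 8.4% |
| 10% | 23.2% | 16.6% |
| 15% | 43.8% | 29.1% |

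The article does not state the allocation; 18:100 is the split in the planning data.

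**6. Upper bound check.** For over-diagnosis alone to produce the planning difference, x = (0.556 − 0.23)/0.77 = 42%.

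**The case against.** The strongest reply is that section 2.2 has two steps, team assessment and then final adjudication, and the article does not describe what the conference sees. A journal article may leave masking and diagnostic criteria to a fuller protocol. This stands in part: a reader might infer that the adjudicators are unmasked, but the text does not say so. What is stated is that the team making the assessment also ascertains infection status, which is more than silence about masking.

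Other objections also stand:

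- The sentence in 2.2 covers infection since enrolment, whereas the grouping variable in Table 1 is previously confirmed COVID-19 history. Knowledge of that earlier history is likely but not stated.
- A reader might infer that neurology alone grades the MRI. Section 2.7 shares the task with neuroradiology, and section 2.10 refers to a neuroradiologic report at both time points.
- A reader might infer that WMH and dementia are dependent by construction. The timing does not support that, since the month-18 scan cannot inform diagnoses at months 6 and 12.
- A reader might infer that the bias must inflate the COVID-19 effect. The Discussion itself lists cognitive impairment or brain fog as a long-COVID symptom, so clinicians aware of infection could attribute decline to it and withhold a dementia label.
- The NIH Toolbox and n-back scores, taken at both visits with neuropsychologist supervision from another department, allow some corroboration. They do not define the endpoint and so cannot remove the bias from it.
- The relabelling shares are assumed. The 42% needed to create the planning difference shows that over-diagnosis alone is unlikely to explain an effect of that size.

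**Conclusion.** The point holds in a limited form. As written, the longitudinal primary outcome is a judgement made by a team that knows about COVID-19 infection, and the month-18 Fazekas grade and dementia status can inform each other. The COVID-dementia and WMH-dementia estimates in section 4.2 are therefore open to differential misclassification, with neither direction nor size fixed by the document.

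On assumed mislabelling of 5–15% in the COVID+ group only and no true effect, the odds ratio runs from 1.23 to 1.77 for over-diagnosis and from 0.94 to 0.81 for under-diagnosis. At 200 patients, over-diagnosis of that order would raise a nominal 5% error to between about 8% and 44%. These figures show sensitivity; they are not estimates of what will happen.

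The documents do not support concluding that the conference is known to be unmasked, that the WMH-dementia link would be an artefact, or that the study's result is invalid. A pre-pandemic baseline read, the month-6 and month-12 diagnoses (as regards the month-18 MRI) and the cross-sectional fNIRS outcome are unaffected. This is an inexpensive improvement worth making while follow-up continues.

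**What to change.** In sections 2.2 and 2.7, for the research endpoint only:

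1. The existing consensus conference decides progression from a case packet with COVID-19 history, test results, infection symptoms and the month-18 MRI report removed. It records the decision before these are released.
2. The Fazekas grades used in the analysis (month 18 and any re-read of the baseline scan) are assigned by the existing neuroradiology team, masked to COVID-19 status and to dementia status.
3. Any unmasking is recorded.

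Clinical care is unchanged. There is no need to bar the treating neurologist from the conference vote, or to strip fNIRS, EEG and DVA results from the packet: nothing in the article shows that those results reach the adjudicators.

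The cost is protocol wording and packet redaction for up to 200 patients, with occasional unmasking to be expected. The conference and the neuroradiology team already exist. If masking is already in place, a sentence in each of 2.2 and 2.7 settles the point.
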